### Study setting

2.1

This is a prospective, single-blind with blind observer, parallel-group design, multi-center, randomized controlled clinical trial. This study will recruit 120 patients with stroke in the subacute phase who are suffering from the upper extremity motor impairment, from five different hospitals in Korea. Participating hospitals are Samsung Medical Center, Seoul; Seoul National University Hospital, Seoul; Bucheon St. Mary’s Hospital, The Catholic University of Korea, Seoul; St. Vincent’s Hospital, The Catholic University of Korea, Seoul; Yongin Severance Hospital, Yongin.

The participants will be allocated into three different study conditions according to their functional reserve, as follows: Study condition (1) participants with preserved ipsilesional CST, confirmed by response of TMS-induced MEPs, Study condition (2) participants with no response of TMS-induced MEPs, but with preserved ipsilesional PM cortex and ipsilesional CST confirmed by DTI, and Study condition (3) participants with no preservation of ipsilesional CST. After the allocation, participants will be randomly assigned to the intervention-group or control-group of each study condition through randomization. The participants of the intervention-group in the three study conditions will receive different protocols of rTMS intervention: Study condition (1) high-frequency rTMS on ipsilesional M1, Study condition (2) high-frequency rTMS on ipsilesional ventral PM, and Study condition (3) high-frequency rTMS on contralesional M1. The participants of the control-group in all three study conditions will receive the same rTMS protocol: low-frequency rTMS on contralesional M1. A schematic diagram is shown in Figure 1.

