### Allocation

2.3

The 120 eligible participants will be allocated into three study conditions based on the functional reserve of each participant, measured by the results of the brain MRI, TMS-induced MEPs, and DTI evaluations. Each condition will consist of 40 patients and they will be randomly allocated into the intervention-group and control-group in a 1:1 ratio. The allocation will be performed by the one researcher of each participating hospital, who will be responsible for the randomization, will not have contact with the participant, and will not be involved in data collection or analysis. The randomization will be done by using a randomization table generated by the www.randomization.com. The randomization sequence will be concealed and only the research principal investigator (PI) will have access authority.

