### Statistical methods

3.5

Demographic and clinical characteristics were reported in terms of frequencies and percentages for categorical variables, while means and standard deviations (SD) were utilized for numerical variables. To compare baseline characteristics of the intervention and control group, an independent t-test and the Wilcoxon Signed-rank test will be used for normally distributed and non-normally distributed variables, respectively. The normality of each variable will be examined using the Shapiro–Wilk test.

All participants undergoing intervention in this study will be included in the intention-to-treat (ITT) set. Safety analyses will be conducted based on the ITT set. Participants who completed all of the evaluation regarding the study protocol will be classified as per-protocol (PP) set. The efficacy analyses will be conducted based on the ITT set. For missing values, data will be analyzed using the Last Observation Carried Forward (LOCF) method. Efficacy analyses well be conducted on the primary and secondary outcomes. For outcome variables, the normality will be examined using the Shapiro–Wilk test. If variables demonstrate normal distribution, a repeated measures analysis of variance (RM-ANOVA) will be used to evaluate the effect of time and groups, including the interaction. If non-normality is found, the Friedman test will be used to determine the differences between the groups. During the analyses, baseline characteristics will be used as covariates for adjustment. In addition, independent t-test or Wilcoxon Signed-rank test will be used to compare parameters between the intervention group and the control group in each condition. Statistical significance will be set at a *p*-value <0.05 for all the analyses.

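### For non-normal outcomes the plan names only related-samples tests (Friedman, Wilcoxon signed-rank), so intervention would not be validly compared with control

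*Protocol article*

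**What the plan says.** All the relevant text is in the protocol article, section 3.5 (Statistical methods).

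- **Trigger:** "For outcome variables, the normality will be examined using the Shapiro–Wilk test".
- **Normal route:** "a repeated measures analysis of variance (RM-ANOVA) will be used to evaluate the effect of time and groups, including the interaction".
- **Non-normal route:** "If non-normality is found, the Friedman test will be used to determine the differences between the groups".
- **Adjustment, stated next:** "During the analyses, baseline characteristics will be used as covariates for adjustment".
- **Arm comparison within each condition:** "independent t-test or Wilcoxon Signed-rank test will be used to compare parameters between the intervention group and the control group in each condition".
- **Baseline comparison:** "an independent t-test and the Wilcoxon Signed-rank test will be used for normally distributed and non-normally distributed variables, respectively".

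The design is set out earlier. Section 2.1 says: "This is a prospective, single-blind with blind observer, parallel-group design, multi-center, randomized controlled clinical trial". Section 2.3 says: "Each condition will consist of 40 patients and they will be randomly allocated into the intervention-group and control-group in a 1:1 ratio". Neither section describes matching or pairing of participants.

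**The concern.** The trial asks whether personalised rTMS does better than the control protocol. The two arms are independent samples, yet both tests named for non-normal data are for related samples.

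This matters because participants are in the subacute phase and all receive conventional rehabilitation (section 2.5), so improvement in both arms is to be expected. A test of change over time would then tend to be significant whether or not the intervention adds anything. The protocol's wording invites that result to be read as a difference between groups.

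The signed-rank test has a different problem. Applied across the arms it is undefined or arbitrary. Applied within one arm it again tests recovery and not treatment.

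The fallback could well be used. A Shapiro-Wilk result decides the route, the Functional Ambulation Category is an ordered category scale (section 3.2), and FMA-UL is capped at 42 at entry (section 2.2).

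**Working it through.** **1. What the sample size assumes.** Inputs from section 3.4: difference 7.25, SD 7.70, power 80%, alpha 5%, follow-up 90%, Lehr's formula.

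- Per arm: 16 × (7.70 / 7.25)² = 16 × 1.128 = 18.05
- After dropout: 18.05 / 0.9 = 20.05
- Two arms × three conditions: 20.05 × 6 = 120.3, which agrees with the stated 120

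The trial is therefore sized for a comparison of two independent arms in each condition. The analysis on either route should make that comparison.

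**2. Stated purpose against what each test does.**

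| Use in section 3.5 | Stated purpose | Test named | What the test needs and tests |
|---|---|---|---|
| Outcomes, non-normal | Group differences | Friedman | At least three related measurements per participant; tests change across visits; no arm term, no group-by-time term, no covariates |
| Each condition, non-normal | Intervention against control | Wilcoxon signed-rank | Matched pairs; tests whether paired differences centre on zero |
| Baseline, non-normal | Intervention against control | Wilcoxon signed-rank | As above |

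Treating the arms as the Friedman columns does not help. There are only two arms, and the software routine refuses fewer than three samples. The covariate adjustment promised in the next sentence cannot be carried out with this test either.

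**3. Friedman when the arms are identical.** Simulation assumptions, which are not in the protocol apart from the SD: four visits, normal data, equal variance and equal correlation of 0.8 between visits, change SD 7.70, no arm effect, both arms pooled in one Friedman test. Eighteen per arm is one condition after dropout (20 × 0.9); 54 per arm is three conditions (3 × 18). The ranges are over repeated runs.

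| Gain in both arms at T1, T2, T3 | 18 per arm | 54 per arm |
|---|---|---|
| 0, 0, 0 | about 5% | about 5% |
| 1.5, 3, 4.5 | 75% to 79% | 99.7% to 99.9% |
| 3, 6, 9 | about 100% | about 100% |

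Run in a single arm of 18 with the smaller gains, the rate was 45%.

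A second model used skewed post-baseline errors, 20 per arm and a mean gain of 7.25 in both arms. Friedman rejected in 100% of 2,000 runs; Mann-Whitney on the T0 to T2 change rejected in 4.7%.

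**4. Signed-rank across the arms.**

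- Unequal arms (20 against 18): the test cannot be computed.
- Equal arms (18 each, normal data, true difference 7.25): the p-value depends on which patients are paired. In about 45% to 53% of simulated trials the verdict at p<0.05 was not the same across 100 random pairings. Two random pairings of the same data disagreed in about 12% to 13%.
- Skewed model (20 per arm): two pairings disagreed in about 5% to 7%.

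**The case against.** The strongest case on the other side has four parts.

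- **Only one branch is affected.** RM-ANOVA with a group term and interaction, and the independent t-test, do compare the arms. That is right, and the point is limited to the non-normal route. How often Shapiro-Wilk would send the analysis there is not known from the protocol.
- **Signed-rank is probably a slip for rank-sum.** The test is offered both times as the alternative to an independent t-test, so this is plausible. With unequal arms the software would expose it, and the baseline use affects no efficacy conclusion. On that reading the Wilcoxon half is a wording correction. The Friedman sentence is not rescued, because it states a between-group purpose outright.
- **The signed-rank figures can mislead.** The 45% to 53% counts trials in which at least one of 100 pairings differed from the others, so it grows with the number of pairings tried. The chance that a single re-sort changes the verdict is the lower figure, 12% to 13%. With equal arms and random pairing the type I error stays near 5%, and the power loss in the normal model was small (73% against 76% for Mann-Whitney). All this stands. What remains is that the p-value is not unique.
- **The Friedman percentages are not type I error.** Friedman correctly detects change over time, and the harm requires someone to report that as a group effect. This stands as a matter of definition, but reporting it that way is what the protocol sentence prescribes.

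A statistical analysis plan that is not shown might settle the matter. However, the protocol names specific unsuitable tests; it does not merely leave the choice open.

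**Conclusion.** The point holds: the text is wrong as written and must be corrected before analysis. On the non-normal route no valid test of intervention against control is named, and this affects the primary outcome. The conclusion follows from the definitions of the tests and from the unpaired parallel-group design; it does not depend on any simulation. The Friedman sentence is the substantive error. The Wilcoxon wording is a smaller one and may be a misnaming.

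The percentages are illustrative. They rest on assumed gains, correlation and error shape, and the Friedman figures on pooling both arms. They show that modest recovery common to both arms would usually produce a significant Friedman result with no treatment difference at all.

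**What to change.** 1. In the baseline sentence and in the sentence on comparing the arms within each condition, name the Wilcoxon rank-sum (Mann-Whitney) test in place of the signed-rank test.
2. Delete the Friedman test. State one fallback for the T0 to T2 comparison that contains the arm term. Rank-based ANCOVA of the change also honours the promised covariate adjustment. Keeping the linear model with robust or permutation p-values is equally acceptable. If the conditions are analysed together, stratify by condition (the van Elteren test if unadjusted). Whether to pool conditions is a separate decision that this correction need not settle.

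Three sentences change. Data collection and patient procedures are unaffected, and the sample size stays at 120 because it already rests on two independent arms. The change should be recorded before any unblinded data are seen.

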### Eligibility criteria

2.2

The inclusion criteria for this study are as follows: (1) hemiplegic stroke (ischemic or hemorrhagic stroke with corresponding lesion determined by MRI or computed tomography scan) patients in the subacute phase (7 days to 3 months from the onset) who are currently hospitalized, (2) Fugl-Meyer Assessment (FMA) score of the upper extremity ≤42, (3) adequate language and cognitive function to perform at least a 1-step obey-command, (4) pre-stroke functional level of modified Rankin Scale (mRS) ≤1, (5) aged ≥19 years old, and (6) patients willing to sign the informed consent. The exclusion criteria are as follows: (1) patients with transient ischemic attack, defined as a rapid-onset focal neurological deficit lasting less than 24 h (42) (2) those with contraindications to rTMS, such as epilepsy, implanted metal objects in the head, or a history of craniotomy, (3) those with progressive of hemodynamically unstable medical conditions, (4) those with coexisting neurological conditions, such as spinal cord injury or Parkinson’s disease, (5) those with major psychiatric disorders, such as major depression, schizophrenia, or dementia, (6) those having contraindications to conduct an MRI study, (7) those who are pregnant or lactating, and (8) patients who have refused to participate in this study.

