### Sample size, recruitment

3.4

Based on the primary outcome of this study and previous literature, we have established the study’s power (1-β) at 80% and a significance level (α) of 5%. The clinically significant effect size (δ) has been designated as 7.25, with an expected standard deviation (σ) of 7.70 (67, 68). Sample size calculation was conducted using Lehr’s formula, with an expected follow-up rate of 90% (68, 69). Finally, the calculated sample size was 120, with each subgroup consisting of 40 participants.

Recruitment of the study participants will be conducted by each participating hospital.

Every research investigator will recruit participants from each hospital who are eligible to participate in the study. Participants will be informed about the current treatment guidelines regarding upper extremity dysfunction in stroke patients, as well as the potential and adverse effects of this study.

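### The within-condition comparison that the sample size rests on is an unadjusted test, so the promised baseline adjustment, including for time since stroke onset, cannot reach it

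*Protocol article*

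**What the plan says.** Four parts of the protocol article bear on this.

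- **Eligibility criteria (2.2)** admits hemiplegic stroke "patients in the subacute phase (7 days to 3 months from the onset) who are currently hospitalized".
- **Allocation (2.3)** states: "Each condition will consist of 40 patients and they will be randomly allocated into the intervention-group and control-group in a 1:1 ratio". Time since onset is not mentioned as a stratum.
- **Sample size (3.4)** states: "The clinically significant effect size (δ) has been designated as 7.25, with an expected standard deviation (σ) of 7.70", and concludes that "the calculated sample size was 120, with each subgroup consisting of 40 participants".
- **Statistical methods (3.5)** names a repeated-measures ANOVA for the outcomes, or a Friedman test if normality fails. It then says that baseline characteristics will serve as covariates, without naming them. As an addition, it says: "independent t-test or Wilcoxon Signed-rank test will be used to compare parameters between the intervention group and the control group in each condition". It does not say whether the repeated-measures ANOVA is pooled over conditions or run in each.

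The primary outcome (3.3) is the change in FMA-UL from T0 to T2, that is, over the 2-week intervention.

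**The concern.** Each condition has its own stimulation target, so each asks its own question, and the comparison of intervention with control inside a condition is what answers it. The tests named for that comparison take no covariates. The adjustment promised one sentence before therefore cannot apply to it as written.

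Time since onset is the natural covariate here. The entry window is wide, and all participants receive inpatient rehabilitation during the 2 weeks. Someone entering in the second week may have more recovery still to come, with either treatment, than someone entering in the third month. With 20 per arm, the arms can differ by chance in mean time since onset, and an unadjusted comparison then carries part of that difference into the estimated rTMS effect. Days since onset must be known to confirm eligibility, so the information is already held and goes unused.

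**Working it through.** **1. Which comparison the sample size supports.** Inputs from section 3.4: difference 7.25, SD 7.70, Lehr's formula, 90% follow-up.

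- Per arm: 16 × (7.70/7.25)² = 18.05.
- With 90% follow-up: 18.05/0.9 = 20.05, taken as 20 per arm.
- Per condition: 2 × 20 = 40. In total: 3 × 40 = 120.

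This reproduces the stated figure. The 120 is three copies of one unadjusted two-group comparison within a condition, with about 18 completers per arm.

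**2. Size of a chance imbalance in time since onset.** The document gives no onset distribution. Assumption: uniform entry over 7 to 91 days.

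- SD = 84/√12 = 24.2 days.
- SE of the difference in arm means = 24.2 × √(2/20) = 7.7 days; 95% range about ±15 days.
- P(imbalance of at least 10 days) = 2 × [1 − Φ(10/7.67)] = 19% per condition.

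Requiring that patients be in hospital may cluster entry, so the SD was varied:

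| Assumed SD (days) | SE (days) | P(≥10 days), one condition | P(≥10 days), at least one of three |
|---|---|---|---|
| 15 | 4.7 | 3.5% | 10% |
| 20 | 6.3 | 11% | 30% |
| 24.2 | 7.7 | 19% | 47% |

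The last column is 1 − (1 − p)³.

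**3. Effect of a 10-day imbalance, and the gain from adjustment.** The document gives no recovery slope. Assumption: the 2-week gain falls linearly by 3, 6 or 9 FMA-UL points from day 7 to day 91.

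- Shift = 10 × fall/84.
- Share of variance explained = (fall/84 × 24.2)²/7.70².
- Power: noncentral t, two-sided 5% (sidedness is not stated), 18 per arm, SD = 7.70 × √(1 − share). Without adjustment it is 78.4%.

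| Fall across window (points) | Shift at 10 days (points) | Shift as share of 7.25 | Variance explained | Power after adjustment |
|---|---|---|---|---|
| 3 | 0.36 | 5% | 1.3% | 78.9% |
| 6 | 0.71 | 10% | 5.1% | 80.4% |
| 9 | 1.07 | 15% | 11.4% | 83.0% |

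These powers keep the t-test's 34 degrees of freedom. Charging two for the covariates (32) gives 78.7%, 80.3% and 82.9%, so the ordering does not change.

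The SE of the treatment contrast with 18 per arm is 7.70 × √(2/18) = 2.57 points. The shifts above are thus 0.14 to 0.42 of a standard error.

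**4. Behaviour averaged over randomisation.** Simulated two-group t-tests with 20 per arm, and a uniformly distributed covariate explaining 10% to 30% of the variance, gave type I error of 4.9% to 5.1% and a mean error close to zero.

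**The case against.** The strongest reply has four parts.

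- **Adjustment is planned.** The covariate sentence speaks of the analyses in general, and the t-test or Wilcoxon comparison comes after it as an extra. If the repeated-measures ANOVA is run in each condition, an adjusted within-condition answer may already exist. This stands in part: a reader might infer that the plan has no adjustment at all, and the text does not support that. But no reading lets the named two-group tests carry covariates, and the Friedman fallback cannot carry them either.
- **The unadjusted test is valid.** A reader might infer that it is biased. It is not: step 4 shows that it keeps its level and averages to the right answer. Spread due to onset time is ordinary residual variance, which its standard error already reflects. What remains is lost precision, and a shift only when an imbalance has actually occurred.
- **The gain may be small.** At the shallow end of the assumed slopes it is half a percentage point of power. Randomising within conditions defined by motor evoked potentials and tract integrity already controls part of prognosis. Both points are fair, and they limit how much weight the finding can bear.
- **Naming covariates is work for the analysis plan.** That is true of the covariate list. The choice of a test that cannot use any covariate is made in this document.

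**Conclusion.** The point holds as a matter of efficiency and robustness to chance imbalance, not of validity. The contrast that fixes the sample size is analysed with a method that cannot use the baseline information the same paragraph promises to use.

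The size depends on two assumptions that the document does not supply: the spread of onset times and the decline in 2-week gain across the window. That gains fall with time since onset is itself assumed. Over the ranges shown, a 10-day imbalance moves the effect by 0.4 to 1.1 points, and adjustment for onset adds 0.5 to 4.6 percentage points of power.

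A reader might also join the 47% chance of a 10-day imbalance in at least one condition to the shift from a 15-day imbalance (0.5 to 1.6 points). These do not belong together. At an SE of 7.67 days, 15 days is reached with probability about 5% per condition and 14% in any of three, and the 47% holds only for uniform entry. This is a worthwhile improvement at almost no cost; the trial is sound without it.

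**What to change.** Replace the per-condition t-test or Wilcoxon comparison of FMA-UL with a pre-specified ANCOVA in each condition: T2 FMA-UL on arm, T0 FMA-UL and days from stroke onset to T0 as a continuous term. Use the same covariates for the T1 and T3 comparisons. With T0 in the model, the arm coefficient is the same whether T2 or the change from T0 is the response, so the primary outcome is untouched.

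The cost is a change of wording and two degrees of freedom per condition, with no extra patients or data. Leave the randomisation lists alone: splitting them by early and late entry, with 40 patients per condition over five hospitals, would make strata very thin, and the covariate already does the work.

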### Data management and monitoring

3.6

All data will be collected using standardized electronic Case Report Form (eCRF) and study participants will be identified only by a research-specific serial number. All personal information and collected data of participants will be maintained in confidentiality under the responsibility of research PI of each participating hospital. All personal information and collected data of participants will be maintained in confidentiality under the responsibility of the research PI of each participating hospital. They will be stored in password-protected files and kept in a locked facility. Routine supervision of the data will be conducted by one of researchers in each participating hospital, independent of other research investigators. Data analysis will be conducted by data analysts, independent of other research investigators. PIs will meet every month to review the implementation of this study. There are no conflicts of interest among all participating researchers.

